**Figure 1 F1:**
[figure not shown]
Study flow chart.

**Table 1 T1:** Clinical trial schedule and observation items.

Period		Screening^∗^ and Baseline	Treatment										Post Treatment	Early termination
Visit	Acupotomy + NBT group	Visit 1	Visit 2	Visit 3	Visit 4	Visit 5	Visit 6	Visit 7	Visit 8	Visit 9	Visit 10	Visit 11	Visit 12	Drop-out
	NBT group	Visit 1			Visit 2		Visit 3			Visit 4		Visit 5	Visit 6	
Day		0	1–3	4–6	7–8	9–11	12–14	15–17	18–20	21–22	23–25	26–28	56–58	
Written consent form		√												
Demographic survey		√												
Medical history, other medical history, and medication administration history		√												
Screening test^†^		√												
Selection/exclusion criteria		√												
Randomization (assignment of registration number)		√												
Physical examination and evaluation of vital signs		√	√	√	√	√	√	√	√	√	√	√	√	√
Medication administration history evaluation^‡^			√	√	√	√	√	√	√	√	√	√	√	√
Treatment	+ Acupotomy (combination treatment group)		√	√		√	√	√	√		√	√		
	NBT (all patients)				√					√				
Primary endpoint evaluation^§^		√					√					√	√	√
Secondary endpoint evaluation^||^		√					√					√	√	√
Exploratory efficacy evaluation^¶^													√	√^#^
Economic feasibility evaluation – cost evaluation^∗∗^		√					√					√	√	√
Adverse reaction monitoring			√	√	√	√	√	√	√	√	√	√	√	√
Economic feasibility evaluation – safety evaluation^††^			√	√	√	√	√	√	√	√	√	√	√	√

∗ One and 2 weeks are required from screening test to active treatment for combination treatment and NBT single treatment groups, respectively.

† Blood test [CBC 5 types, AST, ALT, ALP, albumin, BUN, protein, creatinine, total cholesterol, fasting glucose, RA, CRP, ASO, ESR, electrolyte 4 types (Na, K, Cl, T- CO_2_)]. It can replace test values performed within 8 weeks from screening.

‡ Concomitant medication history and adverse events monitoring are conducted at every visit for treatment and assessment.

§ ODI assessment.

|| Lower back and lower extremity pain (NRS) related to sacral neuropathy, quality of life (European Quality of Life 5 Dimension), Korean version of shortened MPQ, and Korean version of RMDQ.

¶ Additional NBT or surgical treatment within 4 weeks of the final procedure.

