# Exploratory evaluation is not conduced for patients who have completed treatment early. For patients who dropped out of the study, exploratory evaluation is conducted after 4 weeks from dropping out (exploratory effectiveness evaluation for dropout participants can be conducted through telephone counseling instead of in-person visits).

∗∗ Evaluation of direct non-healthcare, direct non-healthcare, and lost productivity costs.

†† Those patients who reported adverse reactions will complete EQ-5D by recalling time of adverse events.

Patients who undergo 1 NBT and show continued symptoms (patient's subjective pain improvement is less than 50% after the procedure or the numeric rating scale (NRS) score being 5 or higher) will undergo screening at 1 week after the first procedure. For screening, demographic information, medical history, physical examination, vital signs, questionnaire survey, laboratory test, and selection/exclusion criteria will be evaluated. Randomization and group allocation will be performed at screening and baseline. Fifty patients will be enrolled and randomly divided into 2 groups. Patients who are judged suitable for the study after the screening test and voluntarily agree to participate will be randomly assigned to either the NBT single treatment group (usual care group) or NBT + deeply inserted acupotomy treatment group in a 1:1 ratio (Fig. 1). Thereafter, the randomly assigned patients will undergo primary and secondary outcome evaluations and economic evaluation.

The NBT + deeply inserted acupotomy group will receive 8 acupotomy treatments (at visits 2, 3, 5, 6, 7, 8, 10, and 11) for 4 weeks as well as additional 2 NBTs (at visits 4 and 9) for 4 weeks. Then, the group will be followed-up for 4 weeks after the intervention treatment. The standard care group will undergo two NBTs (at visits 2 and 4) for 4 weeks and will be followed-up for 4 weeks after the intervention treatment. Primary and secondary outcomes, economic evaluation, and assessment of drug administration history will be conducted at visits 1, 6, and 11, and at the end of follow-up. To evaluate safety, evaluation of adverse events, vital signs, and economic feasibility will be conducted at every visit from visit 2 to visit 12. Laboratory tests will be conducted only at screening.

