### Rescue therapy and concomitant medications

2.7

If severe unbearable pain is observed at the time of visit for screening, limited anti-inflammatory analgesics and muscle relaxants, excluding opioid analgesics and anesthetics, are permitted at the discretion of the clinical investigator providing the NBT (Medications for the digestive system are also allowed to reduce the side effects of rescue medications.). If rescue medications are used, the date and dosage of administration must be recorded in the patient journal.

The types of available rescue medications include skeletal muscle relaxants, anti-convulsant, anti-inflammatory drugs, analgesics, neuralgia drugs, anti-depressants, nonopioid analgesics, antipyretics, weak opioids, and digestive medications.

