#### Safety and adverse events monitoring

2.8.5

1.Physical examination will be conducted and vital signs will be collected at every visit after randomization. The results of the physical examination and vital signs will be reviewed to determine the normality and abnormality of each examination.2.Patient Reported Outcome-Common Terminology Criteria for Adverse Events (PRO-CTCAE)CTCAE evaluated by the medical staff involves assessment of symptoms by the clinician, and this may lead to the omitting or underestimation of side effects experienced by the patients. Therefore, the importance of patients directly explaining their overall health status is increasingly emphasized. In this study, the PRO-CTCAE^[22]^ questionnaire will be used to assess patient safety. It is expected that the main side effect of neuropathic pain treatment will be aggravation of pain. Thus, terms of pain-related symptoms in the PRO-CTCAE will be selected and used to construct a questionnaire. The assessment will be conducted at 2, 4, and 8 weeks.3. Evaluation of objective and subjective symptoms as well as adverse reactions will be conducted at every visit after randomization.-The investigator must record all adverse reactions and concomitant medications used during the clinical trial.-Adverse reactions and concomitant medications will be recorded in the case record form. For adverse reactions, the symptoms, signs, duration (start date/end date), severity, outcome, seriousness, causal relationship with the intervention, and actions taken for the reaction will be recorded.-Symptoms or signs that are present before participation in the study will not be recorded as adverse reactions. However, changes in the frequency, severity, and scope of the symptoms after participation in the study will be recorded as adverse reactions.-Additionally, the name of ingredients, dosage, administration period, and reasons for administration of concomitant medications will be recorded in detail.

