**Demographic information and pre-treatment characteristic analysis method**
Descriptive statistics will be conducted for demographic information and characteristics. Continuous data will be expressed using the number of observations, mean, standard deviation, median, 25% quantile, and 75% quantile. Categorical data will be expressed using frequency and percentage. For continuous data, independent *t*-test will be conducted to test the mean difference between groups if normality assumption is satisfied. If normality assumption is not satisfied, Wilcoxon's rank sum test will be conducted. Chi-Squared test will be conducted to test the mean difference between groups. If more than 25% cells have an expected frequency of less than 5, Fisher's exact test will be conducted.
2.

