**Efficacy evaluation**
In the efficacy evaluation, ITT will be treated as the main analysis group, and PP sets will be treated as the secondary analysis group. All statistical analysis will be conducted as two-sided tests with a significance level of 5%. Two-sided 95% confidence interval will be presented. Descriptive statistics will be presented for each treatment group and visit. Descriptive statistics and 95% confidence intervals will be presented for differences between the baseline and each visit.

Among efficacy evaluation variables, missing values of continuous variables will be analyzed using baseline observation carried forward correction.

A. Analysis of primary endpoints

For symptoms of lumbosacral radiculopathy at each measurement time point, descriptive statistics (number of patients, mean, and standard deviation) of the ODI score and changes in ODI at the end of treatment (4 weeks) and follow-up (8 weeks) compared with the baseline will be presented.

Paired *t*-test or Wilcoxon's signed ranked test will be conducted for intra-group changes in ODI at the end of treatment (week 4) compared with the baseline (0) depending on the satisfaction of normality. An analysis of variance model that includes changes in ODI at the end of treatment compared with the baseline as effects and baseline ODI as covariates will be used to evaluate the effects in the treatment group compared with the control group. Differences in least-square mean between treatment and control groups will be calculated, and two-sided 95% confidence interval and *P* value for the differences will be presented.

B. Analysis of secondary endpoint

Changes in ODI at follow-up (8 weeks) compared with baselineAssessment of subjective pain intensity in patients with lumbosacral radiculopathy-Lumbosacral radiculopathy pain will be divided into lower back and lower extremity pain using NRS, MPQ, and K-RMDQAssessment of quality of life related to lumbosacral radiculopathy-Evaluation of overall quality of life using EQ-5D. The same analysis methods for primary endpoints will be used to analyze secondary endpoints

C. Exploratory efficacy evaluation

Evaluation related to additional NBT or surgery after completion of the study

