**Rate of early termination = (patients who completed the study early/patients who completed the entire study)∗100**

Analysis of rescue medication use

Independent t-test or Wilcoxon's signed rank test will be conducted to compare the number and dose of use according to different types of rescue medication between the groups.

D. Classification and post hoc analysis of responders and nonresponders

Definition of responders

(1)Those with a minimal CID decrease of NRS 2.5 from the baseline to the date of evaluation. Therefore, responders will be defined as follows. For example, pain reduction of greater than NRS 2.5 will be defined as CID, and CID will be used to divide patients into responders and nonresponders.(2)Using the previously described criteria, patients who had improved symptoms and completed the study early will be considered as responders.

Post hoc analysis

Adequate post-hoc analysis will be conducted by a statistician for differences in treatment results for each treatment group using the responder and non-responder criteria.

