**3. Safety assessment**

Descriptive statistics will be conducted to analyze PRO-CTCAE questionnaire items, number of adverse events, number of patients with adverse events, severity of events, and causal relationship of adverse events with the intervention for each dose group. Nonparametric methods may be used if necessary.

Vital signs, physical examination results, and subjective complains of patients will be comprehensively reviewed to perform statistical analysis on items that are considered clinically significant by the researcher. Continuous variables will be presented using the number of observations, mean, standard deviation, median, and minimum/maximum values, and differences in the mean between the 2 groups will be analyzed using paired *t*-test or Wilcoxon's signed rank test. Chi-Squared test or Fisher Exact test will be conducted for analysis of adverse events. Moreover, clinically significant changes will be compared between groups through generalized estimating equation analysis to assess statistical significance.

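### Paired tests are named for comparisons between two independent arms: one of two options for rescue medication, both options for continuous safety variables

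*Protocol article*

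**What the plan says.** All places are in the protocol article.

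- **Section 2.2, Study design:** a randomised trial with two parallel arms. No matching of patients across arms is described.
- **Section 2.8.3, Exploratory effectiveness evaluation:** the number, dose, type and timing of rescue medication are to be compared between the two groups.
- **Section 2.9, C. Exploratory efficacy evaluation, rescue medication:** the independent t-test is one option. The other is Wilcoxon's "signed rank test will be conducted to compare the number and dose of use according to different types of rescue medication between the groups".
- **Section 2.9, 3. Safety assessment:** for continuous variables, "differences in the mean between the 2 groups will be analyzed using paired" t-test or Wilcoxon's signed-rank test. The same paragraph adds a between-group analysis of clinically significant changes by generalized estimating equations.
- **Section 2.9, Demographic information and pre-treatment characteristics:** for a difference between groups, the independent t-test is used; if normality fails, Wilcoxon's "rank sum test will be conducted".
- **Section 2.9, A. Analysis of primary endpoints:** the paired t-test or Wilcoxon's "signed ranked test will be conducted for intra-group changes in ODI at the end of treatment".

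**The concern.** The signed-rank test and the paired t-test work on differences within pairs. In a parallel trial, a patient in the combination arm has no partner in the nerve-block arm, so a paired test cannot answer a between-arm question. The plan nevertheless assigns such tests to one exploratory efficacy comparison and to the between-arm comparison of continuous safety variables.

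Someone following the text literally would have to invent a pairing, for example by enrolment order, and the p-value would then depend on that choice. If the two arms had different numbers of patients, the test could not be run at all. For rescue medication the non-parametric branch is the likely one, because counts and doses of rescue drugs are often skewed with many zeros. There the error would sit in the test actually used.

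**Working it through.** **The plan's only design figure.** Section 2.3 sets 20 per group before 20% dropout: 20 / (1 − 0.20) = 25 per group, 50 in total. This reproduces the stated target. The present point does not depend on it, and the plan gives no figure for the comparisons in question.

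**Step 1. Set the four test statements side by side.**

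| Part of section 2.9 | Comparison | Tests named | Suited to it? |
|---|---|---|---|
| Baseline characteristics | between groups | independent t / rank-sum | both yes |
| Primary endpoint, change in ODI | within group | paired t / signed-rank | both yes |
| Rescue medication | between groups | independent t / signed-rank | t yes, signed-rank no |
| Continuous safety variables | between groups | paired t / signed-rank | both no |

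The first two rows show that the plan separates independent from paired comparisons and has the right vocabulary for each. The last two rows depart from that usage. The count of wrong options is 1 of 2 for rescue medication and 2 of 2 for safety.

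**Step 2. What literal use would do.** The data here are simulated and every setting is an assumption: 20 per arm, normal outcomes, true shift 0.7 SD, one fixed data set. The arms were paired at random 5,000 times.

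- Rank-sum test: one p-value, 0.027.
- Signed-rank test: p from 0.002 to 0.19 across pairings, median 0.048, middle 95% from 0.014 to 0.105.

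A second assumed data set had skewed counts (negative binomial, size 1, probabilities 0.30 and 0.18, so means 0.70/0.30 = 2.3 and 0.82/0.18 = 4.6) and 3,000 pairings.

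- Rank-sum test: p = 0.29.
- Signed-rank test: p from 0.010 to 0.48.

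In both cases the data are fixed and only the pairing varies. A pairing fixed without sight of the data would not by itself raise the false-positive rate. The defect is that the result hangs on an arbitrary choice.

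**Step 3. Unequal arms.** With 20 in one arm and 18 in the other, the signed-rank routine returns an error, because there are no complete pairs. Section 2.3 allows for 20% dropout, so equal numbers at analysis cannot be counted on.

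**Step 4. What else depends on these tests.** The between-group test of ODI change at week 4 is a model adjusted for baseline ODI, and the secondary endpoints use the same methods as the primary. Neither relies on the two faulty sentences.

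**The case against.** The strongest reply is that this is a slip of the pen. In the rescue-medication sentence the signed-rank test stands next to the independent t-test, so an independent-samples comparison was plainly meant, and the baseline paragraph gives its proper name. An analyst with no pairs would notice at once. In the safety paragraph, the generalized estimating equation analysis gives a between-group comparison that does not use the paired tests. All of this stands and it limits the weight of the point. It does not remove it: no other passage corrects either sentence, and the estimating equations are planned for clinically significant changes, not for every continuous safety variable. Nor can the safety sentence be read as within-group change, since it speaks of the difference between the two groups.

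A reader might also infer a bias in how rescue use is collected. Table 1 and its footnote say "Concomitant medication history and adverse events monitoring are conducted at every visit for treatment and assessment", which gives 11 visits after baseline in the combination arm (visits 2 to 12) and 5 in the nerve-block arm (visits 2 to 6). Section 2.2 says "assessment of drug administration history will be conducted at visits 1, 6, and 11, and at the end of follow-up". More questioning in one arm could then seem to inflate its recorded use. The documents do not support that conclusion. The section 2.2 list does not say that medication is asked about at those visits alone, and its visits lie within the fuller schedule, so both statements can be followed. For rescue medication, section 2.7 requires that "the date and dosage of administration must be recorded in the patient journal", and section 2.8.5 adds: "The investigator must record all adverse reactions and concomitant medications used during the clinical trial". Dated records of this kind do not depend on how often a patient is asked. Putting a size on any bias would mean assuming away the journal and choosing a recall loss for which the documents give no value.

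**Conclusion.** Wrong as written, and minor. Paired tests are specified for between-arm comparisons in two places, against the parallel design and against the plan's own usage elsewhere. This conclusion needs no numerical assumption; it follows from the design and the wording. The simulated p-values only illustrate what literal use would do and say nothing about this trial's results.

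The reach is small. Rescue use is exploratory, the estimating equation analysis in the safety paragraph stands, and the primary endpoint, secondary endpoints and sample size are unaffected. If the analyst uses the test that the baseline paragraph names, no result is harmed. The differing statements on when medication history is taken are at most an editorial note, with no bias shown.

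**What to change.** - **Section 2.9, rescue medication:** change *signed rank* to *rank sum*. The independent t-test stays, as do the number and dose by type of drug.
- **Section 2.9, Safety assessment:** for differences between the two groups in continuous variables, name the independent t-test or Wilcoxon's rank-sum test in place of the two paired tests. Leave the generalized estimating equation analysis as it is. If within-group change is also wanted, the paired tests can be kept for that purpose, stated separately.
- **Editorial, optional:** bring the medication-history visits in section 2.2 into line with Table 1.

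The cost is a few words. No data, visits, endpoints or sample size change.

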**3. Safety assessment**

Descriptive statistics will be conducted to analyze PRO-CTCAE questionnaire items, number of adverse events, number of patients with adverse events, severity of events, and causal relationship of adverse events with the intervention for each dose group. Nonparametric methods may be used if necessary.

Vital signs, physical examination results, and subjective complains of patients will be comprehensively reviewed to perform statistical analysis on items that are considered clinically significant by the researcher. Continuous variables will be presented using the number of observations, mean, standard deviation, median, and minimum/maximum values, and differences in the mean between the 2 groups will be analyzed using paired *t*-test or Wilcoxon's signed rank test. Chi-Squared test or Fisher Exact test will be conducted for analysis of adverse events. Moreover, clinically significant changes will be compared between groups through generalized estimating equation analysis to assess statistical significance.

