### Sample size calculation

2.3

This is a practical clinical study to assess the effects NBT and deeply inserted acupotomy combination treatment on lumbosacral radiculopathy.

In a previous pilot RCT that compared the therapeutic effects of deeply inserted acupotomy and general acupuncture in lumbar disc herniation patients,^[14]^ considering a 20% drop-out rate, a total of 50 patients (25 each in the acupuncture and deeply inserted acupotomy groups) were included.

In another RCT that compared the effects of deeply inserted acupotomy and general acupuncture in lumbar disc herniation patients,^[15]^ a total of 40 patients (20 each in the acupuncture and deeply inserted acupotomy groups) were included.

The phase 1 preliminary clinical study that will be conducted aims to estimate the mutual effects of NBT and deeply inserted acupotomy combination treatment and assess whether the combination treatment is effective and safe compared with conventional treatment. Thus, the study must be conducted with a minimum number of patients within the limit that satisfies the study purpose. Currently, there is no previous study that has provided the same intervention. Therefore, based on previous studies that provided similar treatment interventions and involved disease groups as in our study, 20 patients were included in each group. Considering a dropout rate of 20%, a total of 50 patients (25 patients in each group) was set as the target sample size.

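### On its natural reading, the safety plan lets a judgement of clinical significance, made on collected data, choose which supplementary safety items are analysed

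*Protocol article*

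**What the plan says.** Section 2.9, item 3 (Safety assessment) first describes PRO-CTCAE items and adverse events without any selection step. It then turns to vital signs, physical examination and patients' complaints, which "will be comprehensively reviewed to perform statistical analysis on items that are considered clinically significant by the researcher".

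Two further sentences matter. The next one says "Continuous variables will be presented using the number of observations, mean, standard deviation, median, and minimum/maximum values" and names a paired t-test or a signed-rank test for the difference between the two groups. The last says that "clinically significant changes will be compared between groups through generalized estimating equation analysis".

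Section 2.8.5 sets out what is collected. Examination and vital signs are obtained at every visit after randomization: "The results of the physical examination and vital signs will be reviewed to determine the normality and abnormality of each examination". For symptoms already present at entry, "changes in the frequency, severity, and scope of the symptoms after participation in the study will be recorded as adverse reactions".

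Section 2.3 states the aim that these data serve: to "assess whether the combination treatment is effective and safe compared with conventional treatment".

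**The concern.** The sentence is a rule, not a silence. It puts review of the data first, a judgement second and analysis third. An item judged not clinically significant has no stated route to analysis under that sentence.

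The trial has an explicit comparative safety aim. For items governed by this sentence, a reader of the results could not tell whether an unreported item showed no difference between arms or was simply not chosen. Selection could draw attention to a chance difference, or leave a real one unexamined. The documents give no sign of which way it would go.

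**Working it through.** **Which data does the rule reach?** Setting sections 2.8.5 and 2.9 side by side:

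- *Adverse events and PRO-CTCAE items:* described and, for adverse events, tested without the filter. Not affected.
- *Complaints recorded as adverse reactions:* these include changes in symptoms present before entry, so they reach the unfiltered analysis. Not affected.
- *Other complaints:* no route to analysis other than the selection sentence. Exposed.
- *Examination findings not recorded as adverse reactions:* section 2.8.5 classes them as normal or abnormal, but this does not define clinical significance. They are not continuous, so the continuous-variables sentence does not rescue them. Exposed.
- *Vital signs:* they depend on the continuous-variables sentence. Section 2.2 says "Laboratory tests will be conducted only at screening", so vital signs are the obvious continuous safety data after baseline, and that sentence can be read as covering all of them. Uncertain.
- *GEE:* exposed if clinically significant changes means items the researcher selected. Not exposed if it means a yes/no outcome compared between arms over visits. Uncertain.

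**Is the choice protected by blinding?** Section 2.6 says the investigator cannot be blinded to treatment, then that blinding is kept when participants are evaluated. It also says that the unblinded sub-investigators have no bearing on results or analysis, and that unblinding follows database closure if the analysis needs it. None of these statements names the choice of safety items or ties it to a blinded stage. The visit counts below also show that masked codes would give little protection if records were reviewed visit by visit.

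**Counts that bear on the fix.** These describe the schedule and the sample size. They would be the same without the selection sentence and do not measure its effect.

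Inputs: 20 per arm after 20% dropout (section 2.3), the visit columns of Table 1, and "8 acupotomy treatments (at visits 2, 3, 5, 6, 7, 8, 10, and 11" (section 2.2). The plan's own sample size reproduces: 20 / (1 − 0.20) = 25 per arm, 50 in total.

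1. Combination-arm post-baseline visits: 2 to 12, which is 11.
2. Visits shared with the NBT arm: combination Visits 4, 6, 9, 11 and 12 (NBT Visits 2 to 6), which is 5. These fall on days 7–8, 12–14, 21–22, 26–28 and 56–58.
3. Combination-only visits: 2, 3, 5, 7, 8 and 10, which is 6. All six are acupotomy sessions, so 6 of the 8 sessions have no NBT counterpart. Only Visits 6 and 11 are both shared visits and acupotomy sessions.
4. Scheduled assessments at full attendance: 25 × 11 = 275 in the combination arm and 25 × 5 = 125 in the NBT arm. Combination-only: 25 × 6 = 150, and 150/275 = 54.5%.

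**Precision at one visit**

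- 95% interval half-width for a difference in means, in SD units, is t(0.975, 2n − 2) × √(2/n). With n = 25: 2.011 × 0.283 = 0.57. With n = 20: 2.024 × 0.316 = 0.64.
- With no abnormal finding in an arm, the exact two-sided 95% upper limit is 1 − 0.025^(1/n). With n = 25: 13.7%. With n = 20: 16.8%.

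Between-arm safety results at this size can only be read descriptively. That favours complete tables over a few selected tests.

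**The case against.** The best defence is that the sentence never says other items will go unanalysed. That is correct: exclusivity is the natural reading, not the literal wording. The sentence on continuous variables carries no restriction and may cover every vital sign. The GEE sentence does not repeat that the researcher decides, and it can describe a yes/no endpoint. Section 2.8.5 sends most new or worsened complaints into the adverse event analysis. A condensed article may also leave item lists, thresholds and the timing of the review to the full protocol or the SAP.

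Most of this stands, and it narrows the point. The absence of an item list or threshold is not the complaint. The selection sentence is, because a SAP that tabulated everything would depart from it as naturally read. Examination findings and complaints outside the adverse reaction record remain exposed even on the readings kindest to the plan.

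A reader might go further and infer an inflated false-positive rate. If the largest of 5 independent null differences were picked and tested at 5%, the chance of a false signal would be 1 − 0.95^5 = 22.6%; with 10 it would be 40.1%. The documents do not support using those figures. They give no number of items, and the stated criterion is clinical significance, not the size of the difference between arms.

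**Conclusion.** The point holds in limited form and is minor. On its natural reading, the safety section lets a judgement made on collected data, and not required to be blind to arm, decide which supplementary safety items are analysed. The exposure is clear for examination findings and for complaints not recorded as adverse reactions. It is possible but not established for vital signs and for the GEE.

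A reader might infer that the trial's safety analysis as a whole is open to selection. It is not: adverse events and PRO-CTCAE items bypass the filter, and the primary ODI analysis is untouched. The effect cannot be quantified, because the documents do not show how many items would be left out. The conclusion rests on reading the sentence as a selection rule, and on section 2.6 not extending blinding to this choice.

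**What to change.** Replace the selection sentence in section 2.9, item 3, as follows:

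- Summarise by arm all collected vital signs (value and change from Visit 1), all examination findings (normal/abnormal shift from Visit 1) and all recorded complaints (number and share of patients with each).
- Give between-arm differences with 95% intervals at the five shared post-baseline visits, read descriptively. Use unpaired methods. This is a deliberate second correction: the arms are independent, so the paired t-test or signed-rank test now named does not apply to a difference between them.
- Summarise the six combination-only visits separately for that arm, with the same items, also descriptively.
- Keep clinical significance as a flag beside the tables. It should decide neither what is summarised nor what is modelled.
- If the GEE is kept, apply it to every vital sign and to abnormal examination (yes/no) at the shared visits, not to selected items.
- Leave the adverse event and PRO-CTCAE analyses as they are.

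The cost is slightly longer safety tables. The data are already collected, so no visit or measurement is added.
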